**4.5 Image Evaluation Approach**

The primary endpoints of this study are PFS and OS. The PFS is evaluated in parallel by an independent image review committee.

**4.6 Handling of Randomization Errors**

If a subject is identified who does not meet the study inclusion/exclusion criteria, or if there is a randomization error due to procedural manipulation, the sponsor's representative and the investigator must discuss whether to continue or withdraw from the trial. Sponsors are required to ensure appropriate record-keeping of such decisions.

**5. Study Drugs**

## 5.1 Drug Information

(1) Anlotinib hydrochloride capsules: Chia Tai Tianqing Pharmaceutical Group Co., Ltd. production  
Specifications: 12 mg/tablet, 10 mg/tablet, 8 mg/tablet;

(2) Anlotinib hydrochloride placebo capsules: Chia Tai Tianqing Pharmaceutical Group Co., Ltd. production  
Specifications: 0 mg/tablet;

(3) TQB2450 injection: Chia Tai Tianqing Pharmaceutical Group Co., Ltd. production  
Specifications: 100 mg/10 mL, 600 mg/20 mL;

(4) TQB2450 placebo injection: Chia Tai Tianqing Pharmaceutical Group Co., Ltd. production  
Specifications: 0 mg/10 mL, 0 mg/20 mL;

(5) Chemotherapy: carboplatin injection: purchased and supplied by Chia Tai Tianqing Pharmaceutical Group Co., Ltd.  
Specifications: 0.1 g;

(6) Chemotherapy: etoposide injection: purchased and supplied by Chia Tai Tianqing Pharmaceutical Group Co., Ltd.  
Specifications: 5 mL: 0.1 g;

The batch number is subject to the drug test report and package.

## 5.2 Medication Management

### 5.2.1 Administration Schedule

Eligible patients with ES-SCLC are randomly assigned to intervention arm 1, intervention arm 2, or control arm. The treatment is divided into the induction stage and the maintenance stage.

#### Stage 1: induction stage (21-day cycle for 4 cycles)

Intervention arm 1: 1200 mg intravenous TQB2450 injection every 3 weeks; 12 mg oral anlotinib once daily on days 1-14; intravenous carboplatin at AUC 5 mg/mL/min on day 1 (the maximum dose was 750 mg); 100 mg/m^2 intravenous etoposide on days 1-3;

Intervention arm 2: 0 mg intravenous TQB2450 placebo injection every 3 weeks; 12 mg oral anlotinib once daily on days 1-14; intravenous carboplatin at AUC 5 mg/mL/min on day 1 (the maximum dose was 750 mg); 100 mg/m^2 intravenous etoposide on days 1-3;

Control arm: 0 mg intravenous TQB2450 placebo injection every 3 weeks; 0 mg oral anlotinib placebo once daily on days 1-14; intravenous carboplatin at AUC 5 mg/mL/min on day 1 (the maximum dose was 750 mg); 100 mg/m^2 intravenous etoposide on days 1-3;

#### Stage 2: maintenance stage (21-day cycle)

Participants with maintenance therapy will be administered until loss of clinical benefit,

unacceptable toxicity, PD, or unsuitable continued medication as determined by the investigators.

Intervention arm 1: 1200 mg intravenous TQB2450 injection every 3 weeks; 12 mg oral anlotinib once daily on days 1-14;

Intervention arm 2: 0 mg intravenous TQB2450 placebo injection every 3 weeks; 12 mg oral anlotinib once daily on days 1-14;

Control arm: 0 mg intravenous TQB2450 placebo injection every 3 weeks; 0 mg oral anlotinib placebo once daily on days 1-14;

During maintenance therapy, patients were allowed to receive PCI, but not radical TR.

**Criteria for dose reduction:**

Anlotinib/placebo: A maximum of two dose reductions of anlotinib (to 10/0 mg, 8/0 mg, and then discontinuation) are allowed according to drug-related AEs, but the cross-dose adjustment is not permitted. For subjects with a dose reduction to 10/0 or 8/0 mg, if subjects may experience disease progression per the investigators but still benefit from the increased dose after a period of medication, subjects could resume only one reduced dose when the safety profile is stable, but the cross-dose adjustment is not permitted.

TQB2450 injection: No dose reduction will be considered.

Efficacy is assessed every 2 cycles. Subjects with disease control and tolerable AEs will continue treatment until loss of clinical benefit, unacceptable toxicity, PD, or unsuitable continued medication as determined by the investigators.

No other antitumor therapies will be considered during the study treatment.

[figure not shown]

### 5.2.2 Drug Distribution, Use, and Recovery

According to the requirements of Good Clinical Practice (GCP), the research medication is governed by hospital custody.

Anlotinib for the test is released and recycled once every cycle. TQB2450 injection is used at the hospitals and is administrated, prepared, injected, and recycled by the major investigator's authorized personnel. Used or partially used drug containers, infusion bags, and syringes can be destroyed on-site according to guidelines and operating procedures established by the research center and local institutions. Unused drugs are returned to the sponsor unless the drug has serious safety problems that require immediate destruction in accordance with local laws and regulations.

Drug administration such as issuance and recycling requires complete records. The recovered drugs should be regularly monitored by the sponsor. Inspectors regularly check the usage and record of the drugs.

## 5.3 Dosage Regimen

### 5.3.1 Administration Method

#### TQB2450/placebo injection:

TQB2450 injection (1200/0 mg) will be diluted with normal saline to a final volume of 250 mL and infused for 60±10 minutes. Patients are administrated with TQB2450 once every 21 days. The infusion time starts with the beginning of the TQB2450 infusion and ends with the completion of

the TQB2450 infusion and normal saline flushing (20 mL normal saline flushing as a recommendation).

Observe the injection for particulate matter and discoloration before dilution. Do not use it if particulate matter or discoloration is confirmed.

Discard normal saline equal to the volume of TQB2450 injection that should be drawn from the 250 mL infusion bag containing 0.9% sodium chloride solution. Add the corresponding volume of TQB2450 injection to the intravenous (IV) infusion bags. Gently invert the solution without shaking to ensure adequate mixing.

The entire contents of the IV bag are intravenously delivered via a 0.2 µm or 0.22 µm in-line filter for 60±10 minutes. Flush immediately after the infusion. The start time and end time of medication will be recorded. If an infusion reaction occurs, appropriate intervention measures should be taken according to the protocol.

Notes: The volume of fluid is extracted in mL for infusion configuration. Different batches of drugs should not be mixed in a single infusion. Ensure that the TQB2450 infusion is transparent, without turbidity and precipitation.

TQB2450 does not contain preservatives and IV bags containing TQB2450 must be used immediately after dilution/mixing. If the TQB2450 dilution cannot be used immediately, the method of storage is as follows:

- ✓ The total storage time from opening the TQB2450 vial to the end of injection should not exceed 6 hours at room temperature;
- ✓ The total storage time should not exceed 24 hours in the refrigerator of 2 °C-8 °C (36 °F-46 °F) without freezing and shaking;
- ✓ Mixing with other medications and intravenous injections should be avoided.

#### **Anlotinib hydrochloride/placebo capsule:**

Before breakfast, take anlotinib orally on an empty stomach, 1 tablet (12 mg)/once/day. Continue the drug administration for 2 weeks and stop for 1 week; thus, 3 weeks (21 days) for a treatment cycle. If there are no special circumstances, medication should be administered at a fixed time every day. If blood collection or safety tests are required, medication should be administered after blood collection. If there are missed medications and the interval from the next medication is <12 h, no medication is supplemented.

#### **Carboplatin injection:**

Dose of carboplatin (mg)=5 (AUC) (mg/mL/min)×[creatinine clearance within 7 days before the first dose (mL/min)+25]

Injection dispensing method and notes:

After calculating the dosage, the product is dissolved with 5% glucose injection at the concentration of 10 mg/mL and then added into the 250-500 mL of 5% glucose injection for intravenous infusion. The product must be used immediately within 8 hours after dilution. The intravenous infusion and

storage must avoid light.

Creatinine clearance Ccr (unit: mL/min) is calculated according to the Scr value of creatinine (calculation formula:  $Ccr = (140 - \text{age}) \times \text{body weight (kg)} / [72 \times \text{Scr (mg/dl)}]$  or  $Ccr = [(140 - \text{age}) \times \text{body weight (kg)}] / [0.818 \times \text{Scr (}\mu\text{mol/L)}]$ ). Attention should be paid to the unit of creatinine in the calculation of creatinine clearance. For women, the calculation result is  $\times 0.85$ .

The U.S. Food and Drug Administration has recommended that physicians should consider setting an upper limit on the dose of carboplatin to reach the required exposure level (AUC) and avoid potential toxicity from overdoses. For patients with normal renal function, the maximum dose is based on GFR, with an estimated upper limit of 125 mL/min. AUC is 5 and the maximum dose of carboplatin is 750 mg.

**Etoposide injection:**

Dosage: 100 mg/m^2 on days 1-3;

Injection dispensing method and notes:

After calculating the dosage, the product is diluted with sodium chloride injection, and the concentration should not exceed 0.25 mg/mL. The intravenous infusion should not be less than 30 minutes.

**Combined administration sequence:****Induction stage:**

On the first day of each cycle, the anlotinib hydrochloride/placebo capsule is first administered orally on an empty stomach, and then TQB2450/placebo injection is intravenously given after at least 5 min, then carboplatin is intravenously given following at least 30 min, and etoposide is finally intravenously given after flushing.

On the second and third days of each cycle, the anlotinib hydrochloride/placebo capsule is first administered orally on an empty stomach, and then etoposide is finally intravenously given.

**Maintenance stage:**

On the first day of each cycle, anlotinib hydrochloride/placebo capsule is first administered orally on an empty stomach, and then TQB2450/placebo injection is intravenously given after at least 5 min.

**Treatment cycle:**

Treatment cycles are repeated every 21 days, with no other anticancer therapy during the medication. Patients with the disease control (CR+PR+SD) and who can tolerate adverse effects continue the medication until disease progression or intolerance.

**5.3.2 Dose Delay and Adjustment Criteria****General principles**

- ✓ The severity of AEs will be graded according to the National Cancer Institute Common Terminology Criteria for Adverse Events (NCI-CTCAE) v5.0 grading system. Given the trial

of the drug combination, the study drugs unrelated to AEs can be identified and the medication regimen can be maintained.

- ✓ When severe toxicity of different severity levels occurs simultaneously, adjustments should be performed according to the highest level observed;
- ✓ When toxic reactions occur, the investigators may refer to the following rules for delay or dose adjustment. Reasons for dose adjustments or delays, the supportive measures taken, and the outcomes will be documented in the patient's chart and recorded on the eCRF;
- ✓ If the investigators determine that the dose adjustment differs from the proposed adjustment rule, the appropriate adjustment will be performed by the investigators regarding clinical practice guidelines or previous clinical experience after consultation and communication with the sponsor; the relevant reasons will be recorded in the subject's medical record;
- ✓ If subjects require permanent discontinuation due to toxic reactions caused by chemotherapy, TQB2450 and anlotinib should be continued until disease progression or unacceptable toxicity (whichever occurs first);
- ✓ If subjects require permanent discontinuation due to immune-related toxicity of TQB2450, anlotinib and chemotherapy should be continued until disease progression or unacceptable toxicity (whichever occurs first).

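### Section 5.3.2 lets chemotherapy run to progression or toxicity after TQB2450 is stopped for immune toxicity, without the four-cycle limit

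*Protocol*

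**What the plan says.** Section 5.2.1 divides treatment into two stages. Carboplatin and etoposide belong to the first, "induction stage (21-day cycle for 4 cycles"). The second, "Stage 2: maintenance stage (21-day cycle"), lists only TQB2450 or placebo and anlotinib or placebo in all three arms. The synopsis gives the same schedule. The maintenance administration sequence in section 5.3.1 agrees: the capsule is taken, "and then TQB2450/placebo injection is intravenously given after at least 5 min", and the sequence ends there.

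The general principles of section 5.3.2 cover what continues when one component is stopped for good. Two parallel bullets deal with this:

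- If chemotherapy is stopped for toxicity, "TQB2450 and anlotinib should be continued until disease progression or unacceptable toxicity (whichever occurs first").
- If TQB2450 is stopped for immune-related toxicity, "anlotinib and chemotherapy should be continued until disease progression or unacceptable toxicity (whichever occurs first").

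**The concern.** The same open-ended stopping rule is attached to different drugs in the two bullets. For TQB2450 and anlotinib it is right, because neither has a cycle limit. For chemotherapy it is wrong, because chemotherapy is a fixed course of four cycles. The ending appears to have been carried from one bullet to the next without adjustment.

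What is at stake is exposure to cytotoxic treatment outside the planned regimen, in patients who have just had an immune toxicity severe enough to end TQB2450 or placebo. Chemotherapy toxicity is substantial in this trial: Table S3 reports treatment-related events of grade 3 or higher in 87.0% of the EC-alone arm. No statistical operating characteristic is touched. The rule is worded identically for every arm and does not enter the sample size, the alpha allocation or the analysis.

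**Working it through.** No design figure is involved, so the check is a comparison of texts followed by a count.

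**Step 1: compare the rules for one patient.** Take a patient who permanently stops TQB2450/placebo for immune toxicity in cycle 2, completes cycle 4, has not progressed and tolerates treatment.

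| Source | Chemotherapy after cycle 4 |
|---|---|
| Synopsis and 5.2.1, induction stage | Ends; four cycles planned |
| Synopsis and 5.2.1, maintenance stage | None listed in any arm |
| 5.3.1, maintenance sequence | None listed |
| 5.3.2, last general principle | Should continue; the only stops are progression and unacceptable toxicity |

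The last row cannot be followed together with the other three.

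**Step 2: look for a cap elsewhere in 5.3.2.** The carboplatin and etoposide rules set the dose levels, allow at most two reductions, require discontinuation after a delay of more than 6 weeks, and give criteria for restarting. None mentions a total number of cycles.

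**Step 3: look for evidence of intent.** Section 1.12 describes the cited first-line atezolizumab trial as giving four cycles of carboplatin and etoposide. Section 4.1.1 takes the control-arm medians from the same source. Four cycles is therefore the consistent intent, but the bullet does not say so.

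**Step 4: bound the number of patients.** Table S3 gives immune-related events leading to benmelstobart/placebo discontinuation:

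- Intervention arm 1: 17/246 = 6.9%
- Intervention arm 2: 2/244 = 0.8%
- Control arm: 3/246 = 1.2%
- All arms: 17 + 2 + 3 = 22; 246 + 244 + 246 = 736; 22/736 = 3.0%

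Only stops during cycles 1-4 create the conflict, and Table S3 does not split the counts by cycle. The range is therefore 0/736 (0%) to 22/736 (3.0%).

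**The case against.** The strongest reply is that the four-cycle limit is fixed in the sections that govern dosing, and that section 5.3.2, which deals with delay and adjustment, should be read subject to them. Several points support this:

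- The first general principle says that "the study drugs unrelated to AEs can be identified and the medication regimen can be maintained", and the regimen to be maintained is the one in 5.2.1.
- The treatment-cycle paragraph in 5.3.1 says patients with disease control "continue the medication until disease progression or intolerance", also without a cap, and nobody would take that to mean indefinite chemotherapy for everyone.
- Section 8.1 bars other antitumour drugs during treatment, naming chemotherapy, and section 3.3 provides for removal of patients given chemotherapy beyond the protocol.
- The section is partly advisory: "the investigators may refer to the following rules for delay or dose adjustment".
- The ceiling of 22 is loose. Some of these patients may have died, progressed or stopped chemotherapy before a fifth cycle could arise. Table S3 shows immune-related events leading to death in 5, 0 and 1 patients by arm, with the overlap not reported.

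Much of this stands as evidence of intent and of small size. It does not repair the sentence. The paragraph in 5.3.1 refers to medication in general, whereas this bullet names chemotherapy, addresses this exact situation and says it should continue. Sections 8.1 and 3.3 deal with treatment outside the protocol, and here the protocol itself directs the continuation. The advisory wording is also qualified: the next principle asks investigators who depart from a proposed adjustment rule to consult the sponsor and record the reason. An investigator who correctly stopped at four cycles could thus look like the one deviating.

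**Conclusion.** The concern holds. The last general principle of section 5.3.2 contradicts the four-cycle induction and the chemotherapy-free maintenance stage, and no other text in 5.3.2 restores the limit. It is a drafting error in an operative dosing rule and should be corrected, though its weight is minor.

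The number of patients it could reach lies between 0 and 22 of 736. That range takes the Table S3 counts as the upper bound and assumes nothing about when the stops occurred. It also reads the bullet, which names only TQB2450, as covering TQB2450 or placebo, as a double-blind trial requires. The documents do not show that any patient received a fifth cycle, and no estimate of extra cycles is possible from them.

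**What to change.** Reword the end of the bullet along these lines:

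> …anlotinib/placebo should be continued until disease progression or unacceptable toxicity, and chemotherapy should be continued up to a total of 4 cycles, or until disease progression or unacceptable toxicity if earlier.

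The preceding bullet, on stopping chemotherapy, can stay as it is. The cost is one sentence in a protocol amendment, with no added patients, procedures or analyses.

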#### **Criteria for Dose Delay of TQB2450**

If the medication is delayed due to AEs caused by TQB2450 injection and cannot be resumed over 12 weeks, TQB2450 injection treatment should be permanently terminated. The management of AEs induced by TQB2450 injection refers to Recommendations for the Management of immune-related Adverse Events (irAEs) Caused by Immune Checkpoint Inhibitor Therapy. TQB2450 dose delays are allowed, but no dose adjustment.

#### **Criteria for Dose Delay and Adjustment of anlotinib**

During the administration period (1-14 days) of anlotinib every cycle, if anlotinib-related AEs occur and the medication needs to be delayed, the maximum delay time should not exceed 5 days. If the medication cannot be continued for more than 5 days, the remaining anlotinib will not be administered in this cycle. Until the start of the next cycle of medication, if the medication can continue to be delayed due to AEs, the maximum delay time shall not exceed 8 weeks.

Patients who remain unable to take anlotinib (including dose reduction) for more than 8 weeks need to permanently discontinue anlotinib (except for events caused by non-safety reasons). Dose delay and adjustment of anlotinib are allowed if necessary during the trial.

When anlotinib-related AEs occur during the trial, the dosages of anlotinib are allowed to be reduced (12/0 mg-10/0 mg-8/0 mg in turn). If the dose of 8/0 mg/d is not tolerated, then treatment should be terminated. If there is potential for disease progression and safety is manageable after the dose is reduced for a period of time, one dose level can be up-regulated to the initial dose from the next cycle.

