|                         | 
Participants with maintenance therapy will be administered until loss of clinical benefit, unacceptable toxicity, progressive disease (PD), or unsuitable continued medication as determined by the investigators. During maintenance therapy, patients were allowed to receive prophylactic cranial irradiation (PCI), but not radical thoracic radiotherapy (TR). The maintenance stage will be administered as follows:
 
Intervention arm 1: 1200 mg intravenous TQB2450 on day 1; 12 mg oral anlotinib once daily on days 1-14;
 
Intervention arm 2: 0 mg intravenous TQB2450 placebo on day 1; 12 mg oral anlotinib once daily on days 1-14;
 
Control arm: 0 mg intravenous TQB2450 placebo on day 1; 0 mg oral anlotinib placebo once daily on days 1-14;
 
Dose reduction:
 
Anlotinib: A maximum of two dose reductions of anlotinib (to 10/0 mg, 8/0 mg, and then discontinuation) was allowed according to drug-related AEs and cross-dose adjustment is not permitted. For subjects with a dose reduction to 10/0 or 8/0 mg, if subjects may experience disease progression per the investigators but still benefit from the increased dose after a period of medication, subjects could resume only one reduced dose when the safety profile is stable and cross-dose adjustment is not permitted.
 
TQB2450: No dose reduction will be considered.
 
Efficacy is assessed every 2 cycles. Subjects with disease control and tolerable AEs will continue treatment until loss of clinical benefit, unacceptable toxicity, PD, or unsuitable continued medication as determined by the investigators.
 
No other antitumor therapies will be considered during the study treatment.
 |

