### 1.10 Safety and Tolerability of Anlotinib with Consecutive 2 Weeks and Stop 1 Week

Safety profiles from 19 completed clinical trials involving 1576 patients exposed to anlotinib were summarized. These patients received anlotinib of the initial dose of 12 mg for 2 weeks, followed by 1-week discontinuation. Common AEs (≥20%) were hypertension, fatigue, hand-foot skin reaction, diarrhea, hyperlipidemia, proteinuria, hypothyroidism, oropharyngeal pain, cough, dysphonia, and various types of bleeding.

The safety profile of anlotinib in advanced NSCLC was primarily obtained from a multicenter, randomized, double-blind, placebo-controlled phase III trial (ALTER0303, n=437) and a multicenter, randomized, double-blind, placebo-controlled phase II trial (ALTER0302, n=117).

The ALTER0303 study enrolled patients with locally advanced/metastatic NSCLC and progression or intolerance following at least two types of systemic chemotherapy. Eligible patients with EGFR mutation or ALK-positive had progression or intolerance following targeted therapy. The Eastern Cooperative Oncology Group performance status (ECOG PS) of patients was 0-1. Patients with bleeding tendencies, poor blood pressure control, abnormal coagulation profile, and 24-hour urinary protein >1.0 g were excluded. A total of 294 patients received 12 mg oral anlotinib once daily on days 1-14 every 3 weeks, and 57.14% (168/294) of the subjects received treatment of  $\geq 6$  cycles. Twenty-five patients (8.5%) in the anlotinib group reduced the dose to 10 mg and three (1.0%) experienced two dose reductions (to 10 mg and then 8 mg). The main AEs leading to dose reduction were hand-foot skin reaction, hypertension, diarrhea, anorexia, oral mucositis, abnormal liver function, proteinuria, hyperlipidemia, and fatigue. The incidence of AEs with all grades in the anlotinib and placebo groups was 97.3% and 88.1%, respectively. The incidence of AEs with  $\geq$  grade 3 in the anlotinib and placebo groups was 47.3% and 18.2%, respectively.

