#### **Table. Dose levels of anlotinib**

| Dose levels | Usage                  | Specific amounts of drugs                      |
|-------------|------------------------|------------------------------------------------|
| 1           | 12 mg oral, once a day | 12 mg anlotinib hydrochloride capsules, 1 pill |
| 2           | 10 mg oral, once a day | 10 mg anlotinib hydrochloride capsules, 1 pill |
| 3           | 8 mg oral, once a day  | 8 mg anlotinib hydrochloride capsules, 1 pill  |

When the non-bleeding AEs occur, dose adjustment can be performed according to the table below for general principles.

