## 10.8 Management of Common AEs

The dose adjustment of anlotinib due to AEs is listed in section 5.3.2. The type and management of irAEs caused by TQB2450 are listed in the Appendix.

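### Section 5.3.2 sends re-escalated anlotinib patients back to the initial dose, which from 8 mg is a two-level step that the synopsis and section 5.2.1 do not allow

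*Protocol*

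**What the plan says.** Under its anlotinib heading, section 5.3.2 first sets the way down: "the dosages of anlotinib are allowed to be reduced (12/0 mg-10/0 mg-8/0 mg in turn". A patient who cannot tolerate 8 mg stops the drug. It then gives the way up. If progression threatens and safety is manageable after a period on a reduced dose, "one dose level can be up-regulated to the initial dose from the next cycle". Nothing limits this sentence to patients on 10 mg.

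The dose-level table that follows runs from level 1, "12 mg oral, once a day", through 10 mg at level 2, to level 3, "8 mg anlotinib hydrochloride capsules, 1 pill". Section 5.3.1 confirms 12 mg once daily as the starting dose.

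The re-escalation rule appears in two other places, each time for patients reduced to either 10 mg or 8 mg:

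- Synopsis, dose reduction: "subjects could resume only one reduced dose when the safety profile is stable and cross-dose adjustment is not permitted".
- Section 5.2.1, criteria for dose reduction: "subjects could resume only one reduced dose when the safety profile is stable, but the cross-dose adjustment is not permitted".

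Section 10.8 points readers to the section with the differing wording: "The dose adjustment of anlotinib due to AEs is listed in section 5.3.2".

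**The concern.** The sentence in 5.3.2 gives two instructions: move up one level, and arrive at the initial dose. They coincide only for a patient on 10 mg. For a patient on 8 mg they name different doses, and the second breaks the rule stated in the synopsis and in 5.2.1.

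The patients concerned are those in whom a dosing error matters most. Because reductions go one level at a time, a patient on 8 mg has been reduced twice for drug-related adverse events. A site that acts on the closing words of the sentence would take that patient in a single step back to the dose that led to the first reduction. Anlotinib also clears slowly: section 1.9.2 gives a mean half-life of 116 h after a single 12 mg dose and says that concentrations build up with repeated dosing. Too large a step is therefore not quickly undone.

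This is a question of patient safety and dosing consistency. It has no bearing on sample size, type I error or power.

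**Working it through.** The plan states no figure to reproduce. The check is to count steps on the protocol's own dose ladder.

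**Inputs**

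- Level 1 = 12 mg, level 2 = 10 mg, level 3 = 8 mg (dose-level table, section 5.3.2).
- Initial dose = 12 mg once daily (section 5.3.1).
- Re-escalation by one level, no cross-dose adjustment, for patients on 10 mg or 8 mg (synopsis and section 5.2.1).

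**Applying the sentence in 5.3.2**

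| Current dose | One level up | Initial dose | Do they agree? |
|---|---|---|---|
| 10 mg | 12 mg | 12 mg (one level) | Yes |
| 8 mg | 10 mg | 12 mg (two levels) | No |

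**Which half is wrong.** The protocol does not define cross-dose adjustment, but beside a limit of one regained dose it most naturally means skipping a level. On that reading the synopsis and 5.2.1 both give 10 mg as the target from 8 mg. The faulty words in 5.3.2 are therefore *to the initial dose*.

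**Size of the step from 8 mg**

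- Permitted: 10/8 = 1.25, an increase of 2 mg or 25%.
- If the initial dose is taken as the target: 12/8 = 1.50, an increase of 4 mg or 50%.
- Excess over the permitted dose: 12/10 = 1.20, or 20%.

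In the control arm the capsules are placebo at every level, so the excess concerns only the two anlotinib arms.

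**How many patients**

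- Section 1.10 reports for the earlier phase 3 monotherapy study in non-small-cell lung cancer that "three (1.0%) experienced two dose reductions (to 10 mg and then 8 mg"; the denominator is 294. 3/294 = 1.02%, with an exact (Clopper-Pearson) 95% confidence interval of 0.21% to 2.95%.
- Section 1.11, on the small-cell monotherapy study, reports 4 anlotinib patients reduced to 10 mg and mentions none at 8 mg.
- Neither study combined anlotinib with chemotherapy. Table S3 gives treatment-related events leading to anlotinib/placebo dose reduction or interruption in 61.4% and 61.1% of the two anlotinib arms. It pools interruptions with reductions, so it cannot serve as a rate of double reduction.

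Only some of the patients who reach 8 mg would later be considered for an increase, so the number exposed to the faulty wording is unknown and probably small.

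**The case against.** The strongest reply is that the safeguard sits in the same sentence. It speaks of one dose level, and the table below it shows that 12 mg is two levels above 8 mg. A reader who follows that half doses correctly, and the synopsis and 5.2.1 say so outright. The closing words may be a translation slip for back towards the initial dose. It is also possible to read initial dose as the dose before the last reduction, since the chemotherapy table in 5.3.2 uses the term in a way that could bear that sense.

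Much of this bears on how likely an error is. It does not make the sentence right. The text does not say towards, and the chemotherapy dose-level table uses initial dose for the starting level, which fits the ordinary meaning of 12 mg here. A dosing rule should not need a charitable reading or a comparison with two other sections.

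Three narrower points do stand:

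- Section 10.8 refers to 5.3.2 for adjustment prompted by adverse events, whereas re-escalation is prompted by threatened progression. The cross-reference is therefore only partial support.
- The general principles in 5.3.2 ask for consultation with the sponsor when an investigator departs from the rule. A step from 8 to 12 mg might trigger it, but a site that believes it is following 5.3.2 would have no reason to ask.
- Returning to a dose that earlier caused toxicity is not in itself the fault. The protocol allows it on purpose, one level at a time, when safety is stable. The fault is the skipped level.

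**Conclusion.** The concern holds. As written, the re-escalation sentence in 5.3.2 cannot be obeyed in full for a patient on 8 mg, and one of its two readings is a two-level, 50% increase where the protocol elsewhere allows one level, 25%. The error is confined to a few words and to patients reduced twice; for patients on 10 mg the sentence is correct. It should be corrected because it is an operative dosing instruction that bears on safety.

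The conclusion rests on two readings: that the initial dose is the 12 mg starting dose, and that cross-dose adjustment means skipping a level. The number of patients affected is not known. The only two-reduction rate in the document, 1.0%, comes from monotherapy in a different disease.

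**What to change.** In section 5.3.2, replace the re-escalation clause with: the dose may be increased by one dose level only (8 to 10 mg, or 10 to 12 mg) from the next cycle; cross-dose adjustment is not permitted.

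This adds no new rule and brings 5.3.2 into line with the synopsis and section 5.2.1, which need no change. The cost is one clause, with no effect on the analysis.
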